**Methods/Design:**

COMPARE study (COzaar in Marfan Patients Reduces aortic Enlargement) is an open-label, randomized, controlled trial with blinded end-points. Treatment with losartan will be compared with no additional treatment after 3 years of follow-up. We will enroll 330 patients with MFS who will be randomly assigned to receive losartan or not. Patients taking beta-blockers will continue taking their standard treatment. The primary end-point is the largest change in aortic diameter at any aortic level measured by means of MRI. Secondary end-points are change in mortality, incidence of dissection, elective aortic surgery, aortic volume, aortic stiffness and ventricular function. We will also investigate gene and protein expression change in the skin under losartan therapy and create prediction models for losartan-treatment response and aortic dilatation.

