## Methods/Design

The COMPARE trial is an open-label, randomized, controlled trial with blinded end-points. Treatment with losartan will be compared with no additional treatment after 3 years of follow-up. We will enroll 330 patients with MFS who will be randomly assigned to receive losartan or not. Patients taking beta-blockers will continue taking their standard treatment. This multi-center study will be conducted in four academic centers in the Netherlands: Academic Medical Center in Amsterdam, University Medical Center St. Radboud in Nijmegen, University Medical Center Groningen and Leiden University Medical Center. A flow chart of the study design is shown in the Figure 1.

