#### Secondary objectives

The secondary objectives are to asses whether losartan influences:

• Mortality, incidence of newly diagnosed dissection in any main vessel and incidence of elective aortic surgery combined into one event endpoint

• Aortic volume measured by means of MRA

• Aortic pulse wave velocity (PWV) and distensiblity measured by means of Magnetic Resonance Imaging (MRI)

• Ventricular function measured by means of MRI

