### Follow-up

After inclusion the following will be obtained during the baseline investigations (V1):

• Patients medical history

• Echocardiography

• MRI or a CT of the heart and entire aorta

• Blood samples

• Punch skin biopsy

Patients will be evaluated after one, two and three years of treatment by means of echocardiography. After 4 weeks and one year of the treatment an additional skin biopsy will be obtained. At every visit, patient's medical history will be obtained. Date of dissection, operation or death will be carefully noted.

The final assessment will be after 3 years of treatment by means of MRI.

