## Statistical considerations

Mean change in aortic diameter in patients with MFS is 0.9-1.5 mm/year[4]. Sample size calculation is based on the primary endpoint (rate of change of aortic diameter). The expected difference between two groups is 0.5 mm/year with a standard deviation of 1.5 mm (2-sided α = 0.05; β = 0.2). Based on these assumptions we calculated that 286 patients are required. To compensate for an estimated 20% drop-out, the inclusion of at least 330 patients is advised.

Primary analyses will be performed on an intention to treat basis. To evaluate the primary end-point a covariate analysis of the diameter change will be used in two groups (no treatment vs losartan) at baseline and after 3 years. Covariate analyses will be also used for the following secondary points: aortic volume, distensibility, pulse-wave velocity, left and right ventricle volumes. "Safety parameters" (i.e. mortality, dissections, surgery) will be evaluated by means of a X^2 ^test.

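### The composite of death, dissection and elective surgery has no stated analysis: the statistics section lists its components as safety parameters for a chi-square test that leaves the recorded event dates unused

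*Protocol article*

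**What the plan says.** All references are to the protocol article.

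- **Secondary objectives.** The list opens "The secondary objectives are to asses whether losartan influences", and its first item is "Mortality, incidence of newly diagnosed dissection in any main vessel and incidence of elective aortic surgery combined into one event endpoint". This is a question about treatment effect on one composite.
- **Statistical considerations.** Covariate analysis is assigned to the secondary points of aortic volume, distensibility, pulse-wave velocity and ventricular volumes. The event endpoint is not in that list. The next sentence labels the events safety parameters: "i.e. mortality, dissections, surgery) will be evaluated by means of a" chi-square test. Three items are named and no combination is mentioned.
- **Follow-up.** "Date of dissection, operation or death will be carefully noted".
- **Drop-out.** It appears once, in the sample size paragraph for aortic diameter: "To compensate for an estimated 20% drop-out, the inclusion of at least 330 patients is advised".

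**The concern.** The trial's only clinical-event endpoint has one construction and role in the objectives (a composite, secondary endpoint) and another in the analysis (three items, safety). A reader cannot tell whether one test or three will be done, or which result answers the secondary objective. In an open-label trial, that choice should not stay open until the data are seen.

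The named test also compares crude proportions. It uses neither event dates nor length of follow-up. If some patients are not followed for events to 3 years, and more so in one arm, the crude proportions differ even when losartan has no effect.

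**Working it through.** **The plan's own figure.** The only sample size is for aortic diameter: 2 × (1.96 + 0.8416)² × 1.5² / 0.5² = 141.3, so 142 per arm and 284 in total. The t-test version gives 143 per arm, or 286, as stated. No event rate or event effect enters it, so no stated figure depends on the chi-square test.

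**Inputs for the event comparison.**
- From the article: 330 patients randomised 1:1, so 165 per arm; 3 years of follow-up; two-sided 5% level.
- Assumed, because the article gives neither: 3-year event risk *p* of 15–25%, and the proportion *d* in each arm lost to event follow-up. Event times are exponential, and loss is uniform over 3 years and unrelated to risk.

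**Expected crude proportion.** Patients who stay contribute *p*. Patients lost contribute the mean risk up to their loss, m = 1 − p / (−ln(1 − p)). So f = (1 − d)p + d·m.

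- *p* = 0.15: m = 1 − 0.15/0.1625 = 0.077. At *d* = 10%, f = 0.135 + 0.0077 = 0.1427. At *d* = 30%, f = 0.105 + 0.0231 = 0.1281.
- *p* = 0.25: m = 1 − 0.25/0.2877 = 0.131. At *d* = 10%, f = 0.225 + 0.0131 = 0.2381. At *d* = 30%, f = 0.175 + 0.0393 = 0.2143.

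**Type I error on all patients.** The standard error is √(f̄(1 − f̄) × 2/165), which is 0.0377 and 0.0461. The spurious differences of 0.0146 and 0.0238 are 0.39 and 0.52 standard errors. Rejection probability is Φ(−1.96 + z) + Φ(−1.96 − z), or 6.7% and 8.1%. With 15% v 25% drop-out the differences halve, z is 0.19 and 0.26, and the result is 5.4% and 5.8%.

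**Patients with an event or full follow-up only.** The proportion is f / (f + (1 − d)(1 − p)). At *p* = 0.15 this is 0.1427/0.9077 = 15.7% v 0.1281/0.7231 = 17.7%. At *p* = 0.25 it is 0.2381/0.9131 = 26.1% v 0.2143/0.7393 = 29.0%. The bias now points the other way.

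**Simulation** (4,000 to 6,000 trials per setting; Monte Carlo standard error near 5% is about √(0.05 × 0.95/4000) = 0.3 points). Paired entries are for 15% and 25% risk unless noted.

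| Setting | Chi-square, all patients | Chi-square, event or full follow-up | Log-rank |
|---|---|---|---|
| No effect, drop-out 10% v 30% | 6.7%, 7.9% | 7.2%, 8.3% | 4.6%, 4.7% |
| No effect, 15% v 25% (risks 5–25%) | about 5–6% | about 5–6% | about 4–5% |
| No effect, 20% in both (risks 5, 10, 20%) | 4.6%, 5.4%, 5.2% | 4.5%, 5.3%, 5.3% | 4.5%, 5.4%, 5.3% |
| HR 0.5, control 10%, losartan 30% | 62%, 85% | 34%, 54% | 49%, 73% |
| HR 0.5, control 30%, losartan 10% | 37% (15% risk only) | 66%, 86% | 51%, 72% |
| HR 0.5, 20% in both | 50%, 72% | not shown | 50%, 73% |
| No effect, 10% v 30%, drop-outs at twice the risk | 5.5%, 5.2% | not shown | 6.9%, 7.8% |

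At 5% event risk with 10% v 30% drop-out, chi-square on all patients gives 5.5% against 4.9% for log-rank.

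**The case against.** Several stronger readings are tempting, and the article does not support them.

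- **That the test ignores the planned 20% drop-out.** The 20% is stated only for the diameter endpoint, which needs an MRI at 3 years. A patient without that scan may still have known event status. The article does not say how patients lost early count in the chi-square test, and a condensed article may leave that to the full protocol.
- **That chi-square costs power.** Taking only 34–54% against 49–73% would suggest so. Those figures belong to one analysis set with more loss on losartan. Swap the arms and the same test rejects in 66–86% of trials. These gaps are bias, not lost power. With equal drop-out nothing is lost.
- **That time-to-event analysis removes the problem.** It does so only if censoring is unrelated to risk. In the last row of the table log-rank is itself inflated, while chi-square on all patients stays near 5% because two errors happen to offset.
- **That the abstract gives a third definition.** It lists "Secondary end-points are change in mortality, incidence of dissection, elective aortic surgery, aortic volume, aortic stiffness and ventricular function" without combining the events, which is ordinary condensation.
- **That deaths are too few for chi-square.** No mortality rate is given, so this is a matter for an exact test if counts prove small.

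A comparison of 3-year proportions with complete follow-up is also a valid analysis. What stands is that the protocol itself names the test, so this is not simply left to an analysis plan, and that the test is attached to something other than the endpoint the objectives define.

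**Conclusion.** The inconsistency is certain and rests on the text alone: a composite secondary endpoint in the objectives, separately listed safety parameters in the analysis, no analysis for the composite, and recorded dates that the named test does not use.

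The statistical consequence is conditional and moderate. It requires event follow-up that is incomplete and unequal between arms. That is plausible when an open-label drug is compared with no additional treatment, but it is an assumption. Under a large split (10% v 30%) and 15–25% event risk, type I error rises to about 7–9%. Under a smaller split (15% v 25%) it is about 6%, and under equal loss there is no harm. The direction depends on which arm loses more patients and on how lost patients are counted. The primary endpoint and the sample size are unaffected. The change should be made, but the trial does not stand or fall on it.

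**What to change.** 1. State the composite once, with the same wording and as a secondary endpoint, in Secondary objectives and in Statistical considerations, and remove the safety label from it.
2. Analyse time from randomisation to first event by log-rank test, with a Cox model for the hazard ratio, censored at last contact.
3. Report death, dissection and surgery separately, with an exact test where counts are small and a p-value is wanted.
4. Seek event status for all randomised patients, including those who stop treatment or miss the final MRI. This matters more than the choice of test, because log-rank does not correct for informative drop-out (about 7–8% type I error if drop-outs carry twice the risk).

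Items 1 to 3 change wording only, since the dates are already recorded. Item 4 costs some follow-up effort for patients who leave the visit schedule.

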## Discussion

COMPARE study will provide important evidence of effects of losartan treatment in adult Marfan patients and lead to evidence-based recommendations. It is of immense importance for this trial to be conducted before Losartan (Cozaar^®^), an existent anti-hypertensive drug, is subscribed to Marfan patients based on promising preliminary results. This study aims to provide further insight in the pathogenesis and genetics of Marfan syndrome unraveling the phenotype-genotype correlation and may provide more evidence based support for the counseling of this group of patients. Insights in the causes and treatment of the aortic dilatation in MFS and therefore the integrity of vascular wall can undoubtedly be extended to other common types of aneurysm.

## List of abbreviations

MFS: Marfan syndrome; TGF-β: Transforming Growth Factor β; AT1: Angiotensin II type 1 receptor; MRA: Magnetic Resonance Angiogram; CT: Computed Tomography; PWV: Pulse wave velocity; MRI: Magnetic Resonance Imaging; ACE: Angiotensin-Converting Enzyme; ARB: Angiotensin Receptor Blockers.
